### Participants and inclusion criteria

2.1

The study protocol was approved by the Brighton and Sussex Medical School Research Governance and Ethics Committee (RGEC; protocols ER/BSMS6337/4 and ER/BSMS6337/6) and conducted in accordance with the ethical standards set by the British Psychological Society and the Declaration of Helsinki. The study recruits two groups of participants: those undergoing working time reduction and control participants who do not change working hours.

We aim to recruit a balanced sample of at least 150 participants for all measures (with approximately half who reduce their working time and half controls). Sample size was determined using a power calculation in G^*^Power on questionnaire pilot data (*n* = 30) with an effect size of 0.45, alpha of 0.05 and power of 0.95. This suggests a group sample size of at least 68 is required. Furthermore, participation in certain study components is voluntary (e.g., MRI, blood sample, interoception, sleep, and time-use diaries), and therefore sample sizes are expected to vary across modalities as a consequence of participant self-selection and differential uptake of specific measures; accordingly, statistical power is also expected to vary between outcome domains. However, as this is the first working time reduction trial to use non-self-report measures, it was not possible to estimate power calculations beyond questionnaire data. In addition, as we will not examine moderating subgroup effects within the control group, fewer controls may be required. The primary purpose of the control group is to account for factors unrelated to the intervention itself, including practice effects, familiarity with the MRI scanning environment, and temporal changes that may occur irrespective of working time reduction. This will allow us to determine whether observed changes in outcomes can be attributed to the working time reduction intervention rather than repeated testing or assessment effects.

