### Model design

3.2

This study uses a longitudinal mixed-effects design with a hierarchical structure. Repeated measures data are nested within employees, who are nested within companies, meaning observations are not independent and will be analyzed using multilevel methods. The design includes one between-subjects factor (group: intervention and control) and one within-subjects factor (time, which will vary per analysis with three datapoint options: baseline and end of trial; baseline, end of trial and 6-month follow-up; and the weekly questionnaires), with an interaction between time and group and corrections for multiple tests. When relevant, employee-level (e.g., age, household income) and company-level (e.g., industry, company size) covariates will be added to statistical models. Table 1 provides a list of all planned covariates. The independent variables will be fixed effects, with up to three random effects: time, employee, and organization. Covariates will be added to the model as fixed effects. This design enables us to determine whether changes are observed across time points for the working time reduction intervention group but not for controls.

**Table 1 T1:** Planned individual-level and company-level covariates for inclusion in statistical models.

Category	Covariate	Type
Individual-level	Baseline value of dependent variable	Continuous
	Gender or sex	Categorical
	Household income	Categorical
	Education level	Categorical
	Age	Continuous
	Living area	Continuous
	Job title	Categorical
	Hours of working time reduction	Continuous
	Remote work status	Categorical
Company-level	Industry	Categorical
	Company size	Categorical
	Trial start month	Categorical
	Profit status	Categorical

The specific coding scheme used for categorical variables alongside any data specific covariates will be specified in future modality-specific preregistrations.

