In line with other working time reduction trials, we will include all participants allocated to the intervention group in the primary analyses regardless of the actual extent of their working time reduction, unless the company average reduction of working hours is < 1 h per week. In which case, their data will be excluded from the main analyses. In secondary analyses, we will investigate whether intervention effects vary by the extent of working time reduction by adding this as a moderator in the mixed-effects models. The extent of working time reduction will be calculated as the difference between participants' self-reported weekly working hours before the trial and during the trial. Working time reduction will firstly be modeled as a continuous variable (hours reduced), but we will also explore potential non-linear relationships using categorical hourly brackets. Additional secondary analyses will investigate whether other individual characteristics moderate the intervention effects, such as sex, age, and baseline score for a given measure. Each potential moderator will be evaluated separately by including the relevant interaction terms in mixed-effects models.

Due to the range of data types and the number of variables, variable-specific hypotheses and model variations (i.e., specific moderators and additional covariates) will be addressed in multiple follow-up preregistrations on the Open Science Framework (OSF). These will provide further details on each data-type analysis within the OSF project repository.

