Nonetheless, this protocol has limitations. Our measures do not capture all factors that may influence responses to working-time reduction. For example, we did not collect information about participants' caregiving responsibilities or other non-work demands, which could moderate the benefits of reduced working hours. These choices reflect the need to minimize participant burden in an already intensive multi-modal protocol by focusing on measures most relevant to the biological mechanisms under investigation, acknowledging that other trials have focused more extensively on social and economic factors (e.g., Gomes and Fontinha, 2024; Lewis et al., 2023). In addition, due to in-person testing requirements, recruitment primarily relied on small to medium employers located near the research site who self-selected into either the working-time reduction or control group. This may limit generalizability to larger or geographically diverse organizations and may also introduce selection effects, as employers with more progressive work cultures were more likely to adopt working time reduction, with considerable variability in how organizations implemented working-time reduction (e.g., fixed vs. flexible days off). It must also be acknowledged that organizations from which participants are recruited self-select into either the working time reduction or control group. Given the need to carefully plan the nature and implementation of working time reduction, randomization of group assignment is not feasible. However, this does increase the likelihood of selection bias, with baseline characteristics in work culture and organizational structure impacting group membership, an issue inherent to working time reduction trials. Therefore, it will not be possible to entirely rule out expectancy effects, that observed benefits of working time reduction are driven by participants' expected improvement over the trial period. However, inclusion of baseline periods in both groups will allow us to observe whether such effects appear before the implementation of working time reduction. Finally, given the complex nature of this protocol and the involvement of the same researchers in both the data collection and analysis processes, it is not possible to entirely blind those performing the analysis to group membership (working time reduction vs control).

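### As most naturally read, section 3.2 enters the Table 1 covariates as main effects, where time-constant covariates cancel from the group-by-time estimate and leave predictors of change unadjusted

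*Protocol article*

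**What the plan says.** Section 3.2 (Model design) describes a multilevel model with one between-subjects factor (group) and one within-subjects factor (time), "with an interaction between time and group and corrections for multiple tests". The time factor takes one of three forms: "baseline and end of trial; baseline, end of trial and 6-month follow-up; and the weekly questionnaires". Baseline is therefore one of the outcome rows in the first two forms, and the weekly series also starts in the baseline weeks (section 2.7).

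On adjustment the section says that employee-level and company-level covariates are added when relevant, and then: "Covariates will be added to the model as fixed effects". Table 1 lists them, including the baseline value of the dependent variable and the hours of working time reduction.

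Interactions with covariates are mentioned only for the secondary moderator analyses: "Each potential moderator will be evaluated separately by including the relevant interaction terms in mixed-effects models".

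The groups are not randomised. The Discussion states that "organizations from which participants are recruited self-select into either the working time reduction or control group", and it accepts that selection bias is more likely as a result.

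**The concern.** In a comparison of self-selected groups, a reader takes the covariate list in Table 1 as the analytic adjustment for differences between the employers and staff who adopt shorter hours and those who do not. For that adjustment to reach the time-by-group effect, the covariates must be allowed to act on change. A main effect acts on level only.

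If the model is fitted as the sentence most naturally reads, a paper could list a dozen covariates and report a group-by-time estimate that is numerically the unadjusted one. A difference in 12-week change that arises because one group has, for example, a different age, income or industry mix would then be counted as an effect of working time reduction. Section 3 is the overall plan for all data types, so each preregistration that adopts the sentence inherits the problem.

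**Working it through.** **The plan's own figures.** Section 2.1 gives a power calculation "with an effect size of 0.45, alpha of 0.05 and power of 0.95" and concludes: "This suggests a group sample size of at least 68 is required". The test is not stated. A paired two-sided t-test with d = 0.45 needs 67 participants, close to 68. A two-sided two-sample t-test with d = 0.45 needs 130 per group. The present point does not depend on this figure. I take from it only the 0.45 as a yardstick, and about 75 per group from "We aim to recruit a balanced sample of at least 150 participants for all measures".

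**The algebra.** For participant i with group G (0/1), time t (0 = baseline, 1 = end of trial), time-constant covariate X and random intercept u:

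Y(i,t) = b0 + b1·G + b2·t + b3·G·t + c·X + u + e(i,t)

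The within-person change is

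Y(i,1) − Y(i,0) = b2 + b3·G + e(i,1) − e(i,0)

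The term c·X has gone, so b3 is estimated as if X had never been entered. The same holds for the baseline outcome value when it is added as a main effect while baseline is also an outcome row, because it too is constant within a person. If X × t is added with coefficient d, the change becomes b2 + b3·G + d·X + error, and b3 is now adjusted for X.

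**Numerical check (simulated data).**
- Two time points, complete data, 75 per group: the group-by-time estimates with and without main-effect covariates agreed to 3e-15, also with the baseline value added. In one simulated trial the estimate was 0.0805 (SE 0.1508) both without the covariate and with its main effect, against −0.033 with covariate-by-time.
- Three-level fit, employees within companies: 0.1187 both ways, against 0.0309 with covariate-by-time terms.
- Balanced 14-week model with random slopes: 0.0904 both ways, against −0.155 with covariate-by-time.
- 20% of end-of-trial values missing at random: the mean estimate moved from 0.254 to 0.256, with a largest single-trial difference of 0.06.

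Some fits gave convergence or boundary warnings. The cancellation rests on the algebra, not on them.

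**What is left unadjusted.** If a covariate differs between the groups by δ SD and predicts change with slope s (SD of outcome per SD of covariate), the bias in b3 is δ × s. The documents give neither quantity, so both are assumed:

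| Imbalance δ | s = 0.1 | s = 0.2 | s = 0.3 |
|---|---|---|---|
| 0.3 SD | 0.03 | 0.06 | 0.09 |
| 0.5 SD | 0.05 | 0.10 | 0.15 |

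The largest value is 0.15 / 0.45 = one third of the planning effect size. In null simulations with 75 per group and no company clustering, the false-positive rate ran from 5.6% to 16.2% over this grid, and returned to about 5% with the covariate-by-time term.

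**ANCOVA is not the same fix.** With complete data at two time points, covariate-by-time terms match a regression of the change score on group and covariates. Regressing the end-of-trial score on group, baseline score and covariates is a different model. Assume no true effect, δ = 0.3, s = 0.2, outcome reliability 0.6 and a stable baseline group difference of 0.3 or 0.5 SD. Covariate-by-time then averages close to 0, the unadjusted contrast about 0.06 (= 0.3 × 0.2), and ANCOVA about 0.12 or 0.20. The ANCOVA figures follow from (1 − 0.6) × 0.3 = 0.12 and (1 − 0.6) × 0.5 = 0.20.

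**The case against.** The strongest reply is that the sentence contrasts fixed with random effects, not main effects with interactions, and that the article defers detail to preregistrations for each data type. Literally this is right. A reader might infer that the plan restricts covariates to main effects; no sentence says so. Main effects remain the natural reading, because the same section names interactions where it wants them: time by group, and the secondary moderators. What it defers is coding, data-specific covariates, moderators and additional covariates. It nowhere says that covariates will act on change. A preregistration could still put this right.

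A reader might also infer that the comparison has no other protection against group differences. That goes too far. The group-by-time contrast removes stable differences in level. Control organisations are intentionally matched on size and sector, although section 2.3 says that precise pair-matching is not feasible. Both groups are offered the same time management training and have a baseline period. What remains is imbalance in characteristics that predict change.

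Nor is the cancellation always exact. Missing values let a little adjustment through. Remote work is asked about for both the pre-trial and trial periods (section 2.8.5), so it could be coded as time-varying. If a preregistration used the baseline value in an ANCOVA on post-baseline scores only, main-effect covariates would adjust; but that is not the model described in section 3.2.

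Finally, the article openly concedes selection bias and does not claim that the covariates resolve it. That is fair, but it does not make the listed adjustment work.

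**Conclusion.** The point holds for the model as section 3.2 most naturally reads. Time-constant covariates entered as main effects cancel from the group-by-time estimate: exactly with complete two-time-point data, almost entirely with missing data. The baseline outcome value cancels too if entered in the same way. The cancellation depends on no assumed figure.

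The size of the resulting bias is unknown. The range of about 0.03 to 0.15 SD rests wholly on assumed imbalances and slopes. Its low end is negligible and its high end is the worst corner of the grid. The documents do not support a claim that the trial's result will be materially biased, or that selection is otherwise uncontrolled. They support the narrower conclusion that the listed adjusters would not adjust the contrast of interest for characteristics that predict change. It should be fixed, and it can be fixed in the preregistrations without touching data collection.

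**What to change.** Replace the sentence in section 3.2, and carry the replacement into each preregistration:

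> A short pre-specified list of pre-intervention covariates (e.g. age, gender, income, education, grouped industry, company size) will enter with their interaction with time, alongside the group-by-time term. The model without these interactions will be reported as the unadjusted result.

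Three points go with it:
- Do not describe this as equivalent to ANCOVA on the baseline score. ANCOVA answers a different question in self-selected groups and can add bias when the groups differ stably at baseline. It may be shown as a sensitivity analysis.
- Keep hours of working time reduction out of the adjustment set, because it is part of the treatment. Its place is the secondary analysis by extent of reduction.
- Leave the one-at-a-time moderator models as they are. They answer a secondary question and do not adjust the primary effect.

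The cost is some degrees of freedom, especially at company level, so industry and company size must be grouped into few categories.

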Participants in the working time reduction group are expected to achieve a “meaningful reduction” in average weekly working time, with original pay maintained (on par with inclusion criteria of recent national cohort trials, e.g., Fan et al., 2025). The majority of participants have switched to a 4-day week, with one full workday reduced each week. However, participants are not required to implement a 4-day schedule, and a minority have adopted other forms of work-time reduction, including a 9-day fortnight with one full workday reduced every other week, two half-days per week, or shorter days. This aligns with recent international cohort trials, in which the majority of participants switched to a 4-day week but were permitted to adopt other schedules according to organizational and individual preferences (Fan et al., 2025). For participants in this group, the research programme is explicitly referred to in recruitment materials as a “*4-day week study*.” Given the heterogeneity of work patterns adopted by employers across the trial, participants undergoing working time reduction will be referred to as the “working time reduction group” throughout this paper.

Control participants do not undergo any reduction in working time between the start and end of the research period. They maintain their original work schedule and pay. For participants in this group, the programme is referred to in recruitment materials as a “*workplace wellbeing study*.” No active deception is used; participants in this group are aware they are part of a larger study in which another group is receiving a reduction in working time.

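### Table 1 lists the delivered dose (hours reduced) as a general adjustment covariate; it should be kept out of the primary models and used only in the secondary dose analyses

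*Protocol article*

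**What the plan says.** All of the following is in the protocol article.

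- **Model design (3.2), covariates.** The text states that "Table 1 provides a list of all planned covariates", and the table is captioned "Planned individual-level and company-level covariates for inclusion in statistical models". One individual-level, continuous row is "Hours of working time reduction". Another row is the baseline value of the outcome. No row is marked as primary or secondary.
- **Model design, how covariates enter.** "When relevant, employee-level (e.g., age, household income) and company-level (e.g., industry, company size) covariates will be added to statistical models", and "Covariates will be added to the model as fixed effects". No criterion for relevance is given and no covariate-by-time term is mentioned. The treatment effect is the group-by-time interaction.
- **Model design, role of dose.** Extent of reduction is defined as self-reported weekly hours before the trial minus those during it. The primary analyses keep intervention participants whatever their reduction, apart from companies averaging under 1 h per week. Secondary analyses then examine "whether intervention effects vary by the extent of working time reduction by adding this as a moderator in the mixed-effects models". The opening of Statistical analysis (3) also puts extent of reduction under the secondary objective.
- **Measures (2.7) and Work pattern questionnaire (2.8.5).** Hours before and during the trial are both asked once, in trial week 12.
- **Participants and inclusion criteria (2.1).** "Control participants do not undergo any reduction in working time between the start and end of the research period".

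**The concern.** Groups are not randomised here, so covariates are needed to deal with differences that existed before the change in hours. Hours reduced cannot do that job. It is measured after the intervention starts, it follows from group membership, and it is the presumed route of benefit: the Introduction cites earlier trials in which larger reductions went with larger gains. A group term adjusted for it describes being in the reduction group while reducing no hours, which is not the trial's question. Where the model lets hours compete with the treatment term, a real benefit could be reported as small or absent, or with a needlessly wide interval. It would also contradict the statement in the same section that the primary analysis sets the extent of reduction aside.

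**Working it through.** **Inputs from the article.** About 75 per group (150 in total), effect size 0.45, hours reduced about 0 in controls. The article gives no figure that depends on this covariate, so there is none to reproduce.

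**Assumptions, not in the article.** The effect of 0.45 is read in SD units and the pre-post correlation is 0.5. Mean hours reduced is 4 to 6 (SD 2 to 4) in the intervention group and 0 (SD 1 to 3) in controls. Clustering by company is ignored.

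**Step 1: the additive form.** Each person has one value of hours, the same at both time points, so as a main effect it cancels from that person's change. With complete two-point data the group-by-time term equals the group difference in mean change, so it cannot move. In 30 simulated data sets fitted with a random-intercept model, the interaction averaged 0.454 (SE 0.164) with and without hours. The largest difference in the estimate was under 1e-14.

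**Step 2: forms in which hours competes with group.** These are an ANCOVA on the end-of-trial score, or a model with hours by time. Write the benefit as b·group + c·hours, with mean reduction m = 6 in the intervention group and 0 in controls. Without hours the group term estimates b + 6c = 0.45. With hours it estimates b.

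- All benefit through hours: c = 0.45/6 = 0.075, b = 0.
- Half: 6c = 0.225, b = 0.225.
- None: c = 0, b = 0.45.

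**Step 3: precision.** The correlation of group with hours is r = (m/2)/√[(s₁² + s₀²)/2 + (m/2)²], where s₁ and s₀ are the SDs of hours in the intervention and control groups. The variance inflation factor is VIF = 1/(1 − r²), and the SE grows by about √VIF when hours carries no benefit.

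- m = 6, s₁ = 2, s₀ = 1: r = 3/√(2.5 + 9) = 0.88, VIF 4.6, SE × 2.1.
- m = 6, s₁ = 4, s₀ = 3: r = 3/√(12.5 + 9) = 0.65, VIF 1.7, SE × 1.3.

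**Step 4: simulation.** 75 per group, 4,000 replicates per row. Cells give estimate (SE), rejection rate at 0.05. G×T is the change-score form, in which adding hours means adding hours by time.

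| m; s₁; s₀ | Benefit through hours | Model | Without hours | With hours |
|---|---|---|---|---|
| 6; 2; 1 | all | G×T | 0.452 (0.164), 0.77 | 0.001 (0.354), 0.05 |
| 6; 2; 1 | all | ANCOVA | 0.453 (0.143), 0.87 | 0.002 (0.308), 0.05 |
| 6; 4; 3 | all | ANCOVA | 0.453 (0.148), 0.86 | 0.000 (0.187), 0.04 |
| 4; 3; 2 | all | ANCOVA | 0.456 (0.149), 0.86 | 0.005 (0.182), 0.05 |
| 6; 2; 1 | none | G×T | 0.448 (0.163), 0.78 | 0.452 (0.353), 0.25 |
| 6; 2; 1 | none | ANCOVA | 0.449 (0.142), 0.88 | 0.451 (0.307), 0.31 |
| 6; 4; 3 | none | G×T | 0.450 (0.163), 0.78 | 0.450 (0.215), 0.54 |
| 6; 4; 3 | none | ANCOVA | 0.450 (0.142), 0.89 | 0.450 (0.187), 0.66 |

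With no benefit through hours, the SE ratios run from 0.187/0.142 = 1.3 to 0.353/0.163 = 2.2. A separate ANCOVA run (m = 6, s₁ = 3, s₀ = 1.5; 3,000 replicates) with half the benefit through hours moved 0.45 to 0.22. Averaging 12 weekly post-baseline scores, adjusted for baseline, gave the same pattern, with the SE about 1.6 times larger.

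**Step 5: missing values.** Hours is asked only in week 12. Anyone without that questionnaire has no covariate value, so even the additive form would drop that person or need a post-baseline dose to be imputed. In the weekly analysis that puts up to 14 weeks of data per person at stake.

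**The case against.** The strongest case is that the article already gives dose its proper place. The primary analysis sets extent of reduction aside, and dose appears under secondary analyses. Table 1 may simply be a master list: it also holds sex or gender, age and baseline score, which the text names as moderators, and a moderator needs its own main effect. Covariates enter only when relevant, model details are left to later preregistrations, and the planned collinearity checks might flag a variable this close to group. In the form the text literally describes, the treatment estimate does not move.

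Much of this stands. A reader might infer that the plan as written removes the intervention effect. The article does not support that: absorption needs an ANCOVA form or an hours-by-time term, neither of which the text states, and full loss also needs all benefit to run through hours. A reader might also extend the point to "Remote work status". The questionnaire records both pre-trial and during-trial values and coding is deferred, so that is unspecified detail, not an error.

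What remains is that the list claims to cover all planned covariates, marks none as secondary-only and gives no test of relevance. Its baseline-value row leaves room for the ANCOVA form in which the harm occurs. The deferral is for specific moderators and additional covariates; nothing says that this row will be withdrawn.

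**Conclusion.** The concern holds in conditional form. Table 1 names a post-baseline measure of delivered dose as a general adjustment covariate, which conflicts with the primary analysis described in the same section.

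The size depends on model form and mechanism. In the additive group-by-time model with complete two-point data the estimate is unaffected, and the cost is confined to people without the week-12 questionnaire. In an ANCOVA or with hours by time, 0.45 SD becomes about 0 if all benefit runs through hours and about 0.22 if half does. If none does, it stays at 0.45 with an SE roughly 1.3 to 2.2 times larger. These sizes rest on the assumed dose distributions and on independent participants. In none of the forms examined did adding hours improve the estimate of the overall effect.

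**What to change.** Remove the hours-reduced row from the covariates of the primary models, or mark it in Table 1 as secondary-only. Add one sentence to Model design stating that hours reduced is used only in the secondary dose-response (moderator) analyses and does not enter any model that estimates the overall intervention effect. The modality-specific preregistrations should carry the same sentence. This needs no new data and no change to data collection, and it loses nothing in the primary analysis.
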